#### Reimbursement

Couples will be reimbursed ZAR80 (approximately GBP 4.00, as of January 2021) for each data collection appointment (baseline questionnaire, 4-weeks follow-up and 4-month follow-up), mirroring what was done in the Uthando Lwethu study. Reimbursement will be by universal cell-phone voucher sent electronically. Transport will be provided to all intervention sessions and data collection visits, so there will be no transport costs incurred by participants.

#### Couples health screening visit

Couples enrolled in the Igugu Lethu study may schedule an appointment for a couples’ health screening visit at any time after the first group session, once they feel ready to participate in HIV testing and counselling together. The health screening visit will only proceed if, on the appointment date, both partners consent to HIV testing together. All other tests offered are optional. The visit will be conducted to avoid days when the female partner is menstruating. If couples report testing for HIV together as a couple at an alternate venue during the Igugu Lethu study, the couple will be encouraged to undergo the couples health screening visit before completion of study participation.

Informed consent will be taken for each of the health screening procedures (HIV test, random blood glucose (RBG) tests, blood pressure and body mass index (BMI) measurements, and self-sampling for sexually transmitted infection testing) at the start of the visit from each couple by the study counsellor.

At the couples health screening visit, height and weight will be measured, and BMI will be calculated for each partner using an electronic scale (Scale Digital BMI 1110H SOAMAA). Blood pressure will be measured by a study counsellor using Brand Axcess BP 1359 devices while the participant is seated, and three consecutive readings will be averaged [35], in line with recommendations by the American Heart Association.

The counsellor will explain the need for self-collected samples to test for chlamydia, gonorrhoea, and trichomoniasis. The counsellor will explain and demonstrate the procedure for obtaining the self-collected vaginal swabs to the female member of the couple and will ask her to self-collect two sequential vaginal swabs behind a medical curtain for privacy. A nurse will be on call if assistance is needed. For men, the counsellor will explain and demonstrate how to obtain a self-collected penile swab, rotating a flocked swab twice around the full circumference of the penis at the *coronal sulcus*, the junction between the glans and the shaft of the penis. A urine sample will be requested for testing *C. trachomatis, N. gonorrhoeae*, and *T. vaginalis* infections. After the sample collection, samples will be transported to a commercial accredited laboratory in cool boxes. The couples health screening questionnaire includes questions on the acceptability of self-sampling.

The counsellor will conduct pre-test couples counselling for HIV prior to taking blood samples from each partner. A push button lancet safety needle will be used to draw blood from the finger for simultaneous HIV testing, random plasma glucose (RPG) using One Call Plus (ref G113–214) test strips: one Call Plus 50: G133–111 LOT 1690533, and a dry blood spot card will be made to conduct an initial screener test for syphilis (*Treponema pallidum* particle agglutination assay (TPPA test). For HIV testing, the nurse will follow a serial testing algorithm for rapid HIV testing according to South African national guidelines. All participants will be first tested with an advanced one-step anti-HIV test, and specimens that are non-reactive will be considered HIV-negative. Any specimens that are reactive on the first test shall be tested again using a diagnostic kit for HIV antibody (colloidal gold) v2 test. Where specimens are reactive on both the first and the second assays, the results will be reported as HIV-positive. Specimens that are reactive on the first assay but non-reactive on the second assay will receive an ELISA laboratory test and be recorded as discordant. Once HIV test results are available for both partners, the couple will receive post-HIV test counselling with the counsellor. Active referral (i.e. the study staff will make an appointment or accompany the participant to an appointment) will be made for HIV.

The counsellor will give all other results with appropriate interpretation, counselling messages and Department of Health information pamphlets to the couple. The NCD counselling messages will be based on WHO Guidelines for Primary Care in Low-Resource Settings [36], and Section 4.1 of the Standard Treatment Guidelines and Essential Medicines List for South Africa-Primary Health Care Level 2018 Edition [37]. The counsellor will use the BMI-based CVD risk Framingham Heart Study tool to calculate for participants their 10-year risk of a fatal or non-fatal cardiovascular event (myocardial infarction or stroke), according to age, sex, blood pressure, presence or absence of diabetes, and smoking status, and will use this score when counselling about lifestyle changes [38]. In addition to lifestyle counselling, active referral to the clinic will be made for individuals who have systolic blood pressure (SBP) ≥ 180 mmHg or diastolic blood pressure (DBP) ≥ 110 mmHg, and a letter of referral (passive referral) will be given to those with moderate hypertension (SBP: 160–179 mmHg, DBP 100–109 mmHg), suggesting they have a repeat blood measure in 2 weeks. For individuals with an RBG result of > 11.0 mmol/L, we will ask questions to determine if they have symptoms indicating diabetes. If their answers indicate symptoms, they will be actively referred to a clinic. If they do not report symptoms, they will be given a letter of referral (passive referral) requesting that the clinic tests their fasting blood glucose level. Local clinics have agreed to receive such referred cases.

A date for the return (STI results) visit will be scheduled before the couple leave the health screening visit. The preferred mode of contact (e.g. telephone call, text or WhatsApp Messenger or in persons) and ideal hours for contact will be recorded for each couple, so that they can be notified whether they need to physically attend their STI results appointment when their STI results and those of their partner become available. Couples will be informed that if we find a curable STI and three attempts to contact them by their preferred mode of contact fail, a study staff member will attempt to find them. Couples who are referred to clinic during the couples’ health screening visit because one or more test results are ‘out of range’, will be asked to return to the appointment in 2 weeks regardless of positive or negative STI results.

#### STI results visit

For all couples who have at least one ‘out of range’ test during the health screening visit, the STI results visit provides an opportunity for the study team to document whether the couple has acted on any referral made, and if not, to counsel them again regarding the benefits of linking to care. Couples will also receive their STI results together at this visit.

The South African STI Management Guidelines (2015) [39] only provide guidance for syndromic management of STIs i.e. treatment based on presenting STI symptoms, with the exception of syphilis treatment guidelines based on laboratory testing. Therefore, we will use the British Association for Sexual Health and HIV guidelines for the treatment of laboratory diagnosed (i.e. asymptomatic) *N. gonorrhoeae, C. trachomatis* and *T. vaginalis* infections by a nurse, which we have used in a recent STI prevalence study in the same province of South Africa [29].

Samples showing a reactive treponemal test may represent past/treated syphilis or active syphilis. Thus, all positive results from the syphilis screener test on DBS will be referred to the PHC for venous blood testing for syphilis.

#### Laboratory procedures

Samples will be transported on the same day to the accredited laboratory. The dried blood spot will be tested for syphilis using a *Treponema pallidum* particle agglutination assay (TPPA test) [40]. Urine from men and one vaginal swab from each woman will be used for testing of *C. trachomatis, N. gonorrhoeae*, *and T. vaginalis* with DNA amplification methods. The remaining extracted DNA from these samples, along with the self-collected penile swab from male partners and the second vaginal swab from female partners, will be stored at − 80 degrees for later microbiome analysis.

After re-suspending and extracting DNA from stored penile and vaginal swabs, a fluorescent dye (Invitrogen QuantIT high sensitivity dsDNA) will be used to calculate DNA mass/volume which will then be extrapolated to mass/swab. A real-time (quantitative) PCR of the bacterial 16S ribosomal RNA gene will be used to estimate the number of bacterial genomes with linear dilutions of a standard.

After re-suspending and centrifuging stored penile and vaginal swabs, we will conduct proteomic analysis with the supernatant. Protein content will be determined using the Quanti-Pro bicinchoninic acid assay kit (Sigma-Aldrich, MO, USA). The samples will be incubated overnight with trypsin (Promega, WI, USA) and the peptides subjected to metaproteomic analysis using liquid chromatography-tandem mass spectrometry on a Q-Exactive quadrupole-Orbitrap MS (Thermo Fisher Scientific, MA, USA) coupled with a Dionex UltiMate 3000 nano-UPLC system (120 min per sample). Proteins will be identified using a custom UniProt database including human and vaginal microbial entries. Taxonomy will be assigned using UniProt and relative abundance of each taxon will be determined by aggregating the intensity-based absolute quantification (iBAQ) values of all proteins identified for each taxon [41].

#### Documenting relationship break-ups in study couples

If a couple breaks up during Igugu Lethu, each partner will be invited to complete a break-up questionnaire over the phone. The questionnaire will document when the couple broke up if they took up the couples’ health screening visit or tested elsewhere for HIV as an individual/couple between their most recent Igugu Lethu data collection visit and the break-up, and whether or not they feel their participation in Igugu Lethu contributed to the break-up. After completing the break-up questionnaire, follow-up of the couple ends, and study staff will no longer contact them. All participants will be provided with referrals to local counselling/support centres.

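### The break-up rule stops all staff contact without exception, which on its face conflicts with the promise to notify couples of STI results and trace those with a curable STI

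*Protocol article*

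**What the plan says.** The section on documenting relationship break-ups invites each partner to a telephone questionnaire. Among other things, it records whether the partners attended the "health screening visit or tested elsewhere for HIV as an individual/couple between their most recent Igugu Lethu data collection visit and the break-up". The rule that follows is: "After completing the break-up questionnaire, follow-up of the couple ends, and study staff will no longer contact them". The only onward provision in that section is referral to local counselling and support centres.

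The section on the couples health screening visit makes separate commitments about STI results:

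- Appointment: "A date for the return (STI results) visit will be scheduled before the couple leave the health screening visit".
- Notification: the preferred contact mode and hours are recorded so that couples can be "notified whether they need to physically attend their STI results appointment when their STI results and those of their partner become available".
- Tracing: couples are told that, if a curable STI is found and "three attempts to contact them by their preferred mode of contact fail, a study staff member will attempt to find them".
- Re-check: couples referred to a clinic for an out-of-range result "will be asked to return to the appointment in 2 weeks regardless of positive or negative STI results".

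The STI results visit section has the two partners receive their results together. It also says that "all positive results from the syphilis screener test on DBS will be referred to the PHC for venous blood testing for syphilis".

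**The concern.** STI samples go to an outside laboratory, so results come after the screening visit. A couple can separate in that interval. If the break-up questionnaire is also completed in that interval, one instruction tells staff to stop contact and another tells them to notify and, if need be, trace. The break-up section itself expects some separating couples to have been screened, so the overlap is foreseeable.

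What is at stake is treatment of a known, curable infection. The STI results visit section equates laboratory-diagnosed gonorrhoea, chlamydia and trichomonas with asymptomatic infection, so a person who is not contacted may have no symptom to prompt care. A reactive syphilis screen that needs clinic confirmation is in the same position. Partner treatment is also one of the article's stated reasons for offering STI tests to couples.

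**Working it through.** **Consistency check.** No planned figure is at issue, so the first step is to compare the instructions for one case: a partner who was sampled, has separated and has completed the questionnaire, with results still pending.

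| Instruction | What staff would do |
|---|---|
| Break-up section | Make no further contact |
| Screening visit section, notification | Contact to say whether attendance is needed |
| Screening visit section, curable STI | Make three attempts, then try to find the person |

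The break-up sentence has two clauses. Ending follow-up already covers the 4-week and 4-month assessments in the Follow-up section. The second clause, on contact, therefore reads naturally as going further. Nothing in the article exempts STI notification from it.

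**Scale.** Inputs from the article (sample size section): 180 couples; uptake by 4 months of 39% (previous intervention arm) to 55% (target); a combined 5% allowance for loss or break-up. Assumptions, because the article gives no figure: a results window of 2 weeks, taken from the return time for referred couples; 10% to 30% of couples with a curable STI; break-ups spread evenly over 4 months = 4 × 52/12 = 17.33 weeks.

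Expected couples in the window = 180 × uptake × break-up proportion × (window ÷ 17.33).

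1. Screened couples: 180 × 0.39 = 70.2; 180 × 0.55 = 99.0.
2. Break-ups if the whole allowance is used: 70.2 × 0.05 = 3.51; 99.0 × 0.05 = 4.95.
3. In a 2-week window: 3.51 × 2/17.33 = 0.41; 4.95 × 2/17.33 = 0.57.
4. With a curable STI: 0.41 × 0.10 = 0.04; 0.57 × 0.30 = 0.17.
5. Chance of at least one such couple (Poisson): 1 − exp(−0.04) = 4%; 1 − exp(−0.17) = 16%.

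**Sensitivity to the window.**

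- 1 week, low end: 3.51 × 1/17.33 × 0.10 = 0.02 couples, a 2% chance.
- 4 weeks, high end: 4.95 × 4/17.33 × 0.30 = 0.34 couples, a 29% chance.

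**Direction of error.** Three simplifications push these figures up: every screened couple is taken to give STI samples, although every test except HIV is optional; the whole 5% is taken as break-ups, although it also covers loss to follow-up; and the questionnaire is taken as completed inside the results window, although any delay in learning of the separation lowers the count. In the other direction, break-ups may cluster after the screening visit, where HIV results are given. The article offers no rate for that.

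**The case against.** The best defence is that the sentence closes research follow-up only. It sits in a section on documenting break-ups, the Follow-up section describes surveys with their own reminder calls and home visits, and a general closing rule need not cancel a specific clinical commitment. An article also condenses a fuller protocol, which may carry an exception. This reading is plausible. But the article states the contact clause without limit, so the point is a conflict between two stated instructions rather than a missing detail. There is also a sound reason to limit contact after separation, since the Risks section recognises tension and possible violence. That bears on how the exception is worded.

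Some stronger readings are tempting, and the document does not support them:

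- **Separated participants lose access to their results.** They do not: the results date is booked before they leave the screening visit, and those referred for an out-of-range result have already been asked to return.
- **A break-up by itself stops contact.** The stop follows the completed questionnaire. That call asks about screening and so gives staff an opening to mention pending results, although the article does not say that they do.
- **Silence will be taken as a clear result.** This is conjecture. Couples are to be told whether or not they need to attend, so silence is not the described signal of a negative test.
- **The trial's results are at risk.** They are not: the primary outcome is uptake of testing at the screening visit, and later contact changes neither that nor the laboratory results.

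Sharing outcomes with the Department of Health, where the participant consents, is a further safeguard. It is partial, because it carries no duty to notify or trace.

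**Conclusion.** The point holds as a wording conflict with a small safety consequence. Read as written, the contact rule prevents staff from keeping the notification and tracing commitment for partners who separate and complete the questionnaire while results are pending. Whether that was intended cannot be told from the article.

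The expected number is below about 0.2 couples with a 2-week window, most likely none in the whole study. This is an upper figure under the 5% allowance and evenly spread break-ups, given the three simplifications above; the STI proportion and the window are assumptions. Severity is minor, and the change is a cheap improvement.

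**What to change.** Replace the sentence in the break-up section with, for example: *After the break-up questionnaire, contact for surveys and intervention sessions ends; staff may still contact each partner individually to give that partner's own pending results, arrange STI treatment or syphilis referral, and complete follow-up of any clinical referral already made.*

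Individual contact matters because the results visit is otherwise set up for the couple together. The permission should include referrals already made, so that the new wording does not shut out the re-check planned at the STI results visit.

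The cost is one sentence and a staff instruction, submitted to the ethics committees as a protocol modification. Preferred contact mode and hours are already recorded at screening. The downside is a few contacts after separation, some possibly unwelcome.

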#### Process evaluation

The acceptability of the intervention and participation will be evaluated during the study. A sub-sample of participants will be invited by study staff to take part in semi-structured process interviews, with a gender-matched interviewer, at various time points during and after the intervention. Participants will be sampled purposively based on gender, age, engagement with the intervention, and engagement with the general couples’ health screening. Topics explored will include experiences of the intervention and perceptions about attending couples testing. We anticipate recruiting a sample of 20–30 participants, ideally including partners from within the same couple. In addition, all participants will be asked process evaluation questions as part of the 4-month questionnaire. Process interviews or focus groups will also be conducted with up to 5 staff members to explore their experiences of delivering the intervention.

### Outcomes

#### Primary outcome

The primary outcome measure is the proportion of couples that take up couples HIV testing as part of a health screening visit during study follow-up i.e. within 4 months from the date of the first group session, compared to the equivalent proportion in the intervention arm of the Uthando Lwethu study (historical controls).

#### Secondary outcomes of the study

The following secondary outcomes will be measured among couples who participated in the couple’s health screening visit:Concordance of HIV test results among couplesUptake of blood pressure (BP) measurement as a coupleConcordance of hypertension diagnosis (defined as > 140/90 mmHg) within couples who take up couple’s BP measurementsUptake of sexually transmitted infection (STI) testing as a coupleConcordance of STI test results within couples who take up couple’s STI testingUptake of random blood glucose (RBG) finger-prick test for diabetes as a coupleConcordance of diabetes diagnosis (defined as RBG > 11.0 mmol/L) within couples who take up the couple’s RBG testingUptake of height and weight measurement for the calculation of body mass index (BMI) as a coupleObesity (BMI ≥ 30 kg/m2) concordance within couplesAcceptability of self-sampling for STI testing, measured using Likert scales asked as part of the couple’s health screening questionnaireDNA yield, and DNA analysis, of the penile swab samples self-collected by men for STI testing, measured using DNA amplification methodsPenile microbiome functional characteristics of male partners using stored penile swabs, assessed using metaproteomics analysesVaginal microbiome functional characteristics of female partners using stored vaginal swabs, assessed using metaproteomics analysesConcordance of results from metaproteomics analyses of penile and vaginal swabs within couples

Additional secondary outcomes are:o.Acceptability of the intervention and study participation using findings from individual, semi-structured process interviewsp.Whether relationship dynamics are factors in achieving the outcome of couples’ uptake of HIV testing together, using relationship scale variables collected at baseline, week 4, and 4 months

### Statistical considerations

#### Sample size, accrual, follow-up

In the Uthando Lwethu study, 39% of the intervention arm (65/168 couples) had taken up testing together for HIV by 4-months follow-up. A sample size of 180 couples in the Igugu Lethu study provides more than 85% power, at the 5% level, to detect a 40% increase in the proportion testing together, i.e. change from 39 to 55% between the two versions of the intervention, and allow for 5% lost to follow-up or break-up by 4-months.

We aim to accrue the sample of couples over approximately 16 months of active recruitment. Given the continued SARS-CoV-2 pandemic, changes in public health and research-related restrictions may mean a slower rate of recruitment. We will recruit in waves and aim to have approximately 20 couples participate in a round of intervention activities, and will continue to conduct intervention rounds until we achieve our goal of 180 couples. We will follow the couples for a total of 4-months from the date of the first group session in each intervention round.

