Between 2012 and 2015, the Uthando Lwethu Study tested the efficacy of an interdependence theory-based behavioural couples-focused intervention to increase participation in CHTC in South Africa among couples who had never tested for HIV together or mutually disclosed their HIV status [8]. Three hundred thirty-two couples were randomised to the intervention arm (168 couples) or the control arm (164 couples). The intervention arm received two group sessions and four couples counselling sessions, focused on problem-solving and communication skills and was highly effective in increasing the proportion of couples that decided to test for HIV together within 9 months after enrolment, (42% v. 12% [*p* < 0.001]) compared to the control group [9]. Concerned that, in a high HIV prevalence and continued HIV incidence setting [10], 58% of intervention couples did not choose to test together during the Uthando Lwethu study, we optimised the Uthando Lwethu intervention using the Person-Based Approach to intervention development and optimisation [11]. The details of the process of optimising the intervention have been published elsewhere [12]. In brief, a qualitative study was conducted with 20 purposively sampled couples who were formerly enrolled in the intervention arm of the Uthando Lwethu Study, and with 5 study staff who delivered intervention components, with the aim of exploring experiences of the intervention and barriers to testing. The past participants sampled included couples who did not attend couples counselling sessions and did not test for HIV together, some couples who attended all couples counselling sessions and tested for HIV together during follow-up, and others who only took up part of the intervention, with or without deciding to test for HIV together. Developing guiding principles and a logic model that showed how the optimised intervention would increase uptake to CHTC ensured that optimisations were grounded in the local context and drew on theoretical constructs [12]. The optimised intervention still involves two group sessions and up to four couples’ counselling sessions but differs from the Uthando Lwethu intervention in session content, involving community members speaking publicly about their HIV testing history and HIV status, and the possibility that the number of counselling sessions provided will be less if the couple engages in couples HIV testing at an earlier point in the intervention.

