### Intervention

The proposed optimised behavioural intervention consists of up to six sessions (one group session in which couples are initially together and subsequently split into single-gender subgroups, a second single-gender group session, and four couples’ counselling sessions). The intervention is hypothesised to provide information and education around HIV testing and treatment, transform couples’ motivation for looking after their health as a couple rather than as individuals, as well as to improve communication, intimacy and trust necessary for mutual decision-making about behaviours related to sexual risk behaviour and testing for HIV.

Couples will not be reimbursed for the intervention sessions as these are perceived to offer a benefit to couples in and of themselves, and this offers a more feasible set-up to scale-up and implement more widely. This is different to the Uthando Lwethu study which offered reimbursement of ZAR50 (approximately GBP 3.00, as of January 2014) per person per session for all intervention sessions.

#### Group session 1

This first group session will be comprised of a half-day workshop focusing on general health issues in couples, including health conditions assessed at the general couples health screening (blood pressure, diabetes, curable STIs, obesity and HIV). Both partners participate together in the first section of the workshop, with approximately 15–20 couples in each group. Subsequently, the couples will be split into male-only and female-only sub-groups to begin discussing sexual health, family planning, HIV awareness, and benefits and barriers to testing. Community members living with HIV and others who have recently tested HIV negative, and have previously spoken publicly about their HIV testing history and HIV status, will be invited to attend and facilitate a dialogue around couples testing and impact on relationships during the single-gender session.

#### Group session 2

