#### Data analysis

Our primary analysis will compare the proportion of couples who test for HIV in Igugu Lethu with the proportion of couples in the intervention arm of the Uthando Lwethu study who tested for HIV within 4-months of follow-up, unadjusted, using a chi-square test. We will also compare this cohort’s baseline characteristics with the Uthando Lwethu cohort’s baseline characteristics. If there are substantial differences, the comparison will be adjusted for these characteristics using logistic regression.

We will also consider the proportion of couples taking up each of the other non-HIV tests offered as part of the couples health screening. We will calculate descriptive statistics and apply chi-square tests to examine concordance in test results within couples and the secondary outcomes listed a)-i). The acceptability of self-sampling for STI testing by men and women will be examined using responses to Likert scales asked as part of the couple’s health screening questionnaire, separately for men and women, and compared within couples.

The content of the intervention is designed to enhance couples’ levels of communication, intimacy, and other positive relationship characteristics. Therefore, we expect that as couples’ levels of positive relationship characteristics increase, they will be more likely to participate in couples HIV testing. To evaluate the extent to which relationship dynamics are associated with couples’ uptake of HIV testing together, we will describe the change in relationship scores between baseline and 4-weeks, and baseline and 4-months. We will test for associations between these score changes and the HIV couples testing outcome using logistic regression. In addition, the acceptability of the intervention and study participation will be explored through thematic analysis using findings from individual, semi-structured process interviews, and descriptive statistics of responses to the process evaluation questions asked of all participants as part of the 4-month questionnaire.

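### The power statement and the unadjusted chi-square test make no allowance for delivery in rounds of about 20 couples, so the stated power and the 5% error rate hold only if within-round correlation is practically zero

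*Protocol article*

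**What the plan says.** The sample size section of the protocol article starts from the earlier Uthando Lwethu (UL) trial, where "39% of the intervention arm (65/168 couples) had taken up testing together for HIV by 4-months follow-up". It then states that 180 couples "provides more than 85% power, at the 5% level, to detect a 40% increase in the proportion testing together", described as a "change from 39 to 55% between the two versions of the intervention", with an allowance for 5% loss or break-up. The comparator is fixed: "Three hundred thirty-two couples were randomised to the intervention arm (168 couples) or the control arm (164 couples").

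The same section says that the team will "aim to have approximately 20 couples participate in a round of intervention activities" and repeat rounds until 180 couples are reached. The Intervention section says that both partners attend together "in the first section of the workshop, with approximately 15–20 couples in each group". The couples then divide into single-gender groups, and session 2 is also run in groups. The Background says that the UL intervention arm had two group sessions as well, but gives no group size.

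Under Data analysis, the primary comparison of the two proportions is "unadjusted, using a chi-square test". The only further adjustment is logistic regression on baseline characteristics if these differ substantially. The article mentions no round term, design effect or intraclass correlation.

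**The concern.** The power figure and the chi-square test both treat couples as independent. The delivery model makes that doubtful. Couples in one round share facilitators, invited community speakers and group discussion. The Discussion section presents the speakers and the earlier single-gender groups as new components meant to make couples readier to test. If group content moves the primary outcome, couples in the same round are exposed to the same influence and their outcomes are likely to be correlated.

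With positive within-round correlation, the chi-square standard error is too small. The test then rejects a true null more often than 5%, and a valid 5% test has less power than stated. The error rate matters more here, because the main claim rests on a non-randomised comparison with historical controls. Logistic regression on baseline characteristics would not repair this, since shared round effects arise after enrolment.

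The article itself states the power and names the primary test, so this is not a detail left to an analysis plan.

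**Working it through.** **Inputs from the protocol.** p1 = 65/168 = 0.3869; p2 = 0.55; n1 = 168; n2 = 180 × 0.95 = 171; 5% level, taken as two-sided; rounds of about 20, so 180/20 = 9 rounds.

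**Assumptions.** The ICC is not in the documents. Cluster size is m1 = 20 for UL (not documented) and m2 = 20 × 0.95 = 19 for Igugu Lethu.

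**Step 1: reproduce the plan's figure under independence.**
Power = Φ[(d − 1.96·s0)/s1], where d = p2 − p1 = 0.1631.
- Pooled proportion = (65 + 0.55 × 171)/339 = 0.4692, so s0 = √[0.4692 × 0.5308 × (1/168 + 1/171)] = 0.0542.
- s1 = √[0.3869 × 0.6131/168 + 0.55 × 0.45/171] = 0.0535.
- (0.1631 − 0.1063)/0.0535 = 1.06, so power = **85.6%**. The stated figure holds.

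**Step 2: allow for rounds.** Design effect DE = 1 + (m − 1) × ICC; effective n = n/DE.
- Example, ICC 0.01 in both cohorts: DE = 1.19 (UL) and 1.18 (Igugu Lethu); effective n = 141.2 and 144.9; s0 = 0.0590, s1 = 0.0582; (0.1631 − 0.1157)/0.0582 = 0.81, so power = 79.2%.
- If only Igugu Lethu is clustered, n1 stays at 168 and power is 82.6%.

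**Step 3: true size of the planned chi-square test.** Size = 2 × [1 − Φ(1.96 × √(V0/V))], with V0 = 1/168 + 1/171 and V = DE1/168 + DE2/171.
- Example, ICC 0.05 in both cohorts: V0/V = 0.519; 1.96 × 0.721 = 1.41; size = 15.8%.

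**Step 4: power with a small-sample reference.** Assume 8 UL groups (168/20 ≈ 8) and 9 rounds, giving 8 + 9 − 2 = 15 degrees of freedom, and replace 1.96 by 2.131 in Step 1. At ICC 0: (0.1631 − 0.1155)/0.0535 = 0.89, so power is 81%.

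Each range runs from both cohorts clustered to Igugu Lethu only clustered:

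| Assumed ICC | Power, normal reference | Type I error of planned test | Power, t on 15 df |
|---|---|---|---|
| 0 | 85.6% | 5.0% | 81% |
| 0.005 | 82.4–84.1% | 6.1–5.5% | – |
| 0.01 | 79.2–82.6% | 7.2–6.0% | 74–78% |
| 0.02 | 73.2–79.5% | 9.4–7.1% | 67–74% |
| 0.05 | 58.4–71.1% | 15.8–10.3% | 51–65% |

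A beta-binomial simulation (40,000 runs per scenario) agrees on the error rate: 7.2–6.1% at ICC 0.01 and 15.5–10.4% at 0.05.

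**Thresholds (normal reference).** Power drops below 85% at an ICC of about 0.001 (both clustered) to 0.002 (Igugu Lethu only), and below 80% at about 0.009 to 0.018. With groups of 15 in both cohorts and ICC 0.01, power is 81–83% and the error rate is 6.6–5.8%.

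**The case against.** The harm depends on an ICC that nobody has measured. Up to four of the six sessions are given to couples one at a time, and each couple decides for itself when to book screening. Both features could keep the correlation low. At 0.005 to 0.01 the damage is modest: power of 79–84% and an error rate of 5.5–7.2%. The UL group size and number of groups are unknown, so clustering in both cohorts is an assumption and not a documented fact. This stands, and it is why the results are given as conditional ranges. Changing COVID-19 restrictions are also mainly a matter of confounding between the cohorts, which the article discusses, and the argument here does not rely on them.

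A reader might also infer that the power claim fails without any clustering. Entering the rounded 39% in place of 65/168 gives about 84% after 5% loss. The documents do not support that reading. The article gives the exact count, and with it the power is 85.6%, loss included. There is no arithmetic error.

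**Conclusion.** The point holds conditionally. The stated power is correct for independent couples, but its margin over 85% is so thin that almost any within-round correlation removes it. The planned chi-square test has no protection against such correlation. The effect is modest at an ICC of 0.01 or below and becomes serious from about 0.02. At 0.05, power is 58–71% and the type I error 10–16%.

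Confidence is high for the mechanism and limited for the size. The size rests on an assumed ICC, UL groups of 20 at one end of each range, and a two-sided test. It would go too far to say that the false-positive rate certainly exceeds 5%: correlation is likely given the delivery model, but the documents do not quantify it.

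**What to change.** - **Analysis.** Make intervention round the cluster in the primary comparison, and UL group too if membership was recorded, which the article does not say. Use cluster-robust or mixed-model standard errors with a small-sample correction, because there are only about 9 rounds. Record round for every couple.
- **Power statement.** Replace the single figure with power over a stated ICC range, computed for the corrected analysis. On about 15 degrees of freedom this is roughly 81% at ICC 0, 74–78% at 0.01 and 51–65% at 0.05. The degrees of freedom assume about 8 UL groups and should be updated once the real number is known.
- **ICC.** Estimate it from the UL groups if those data exist. Otherwise state it as an assumption.

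**Cost.** Changes to the analysis wording, a less favourable stated power, and wider intervals because there are few clusters. No extra couples and no change to how the intervention is delivered.
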